### Intervention

#### Intervention condition

Participants in the intervention arm will receive care as usual as well as the 8-to-12-week PiB intervention [20]. The program was developed with informal caregivers and care professionals at the Alzheimer Centre Limburg (ACL). The self-management program consists of a face-to-face intake session, an online period, and a face-to-face evaluation session with a personal coach. Coaches are care professionals who priorly received a 3-h training in self-management techniques, goal setting, and online help. The development of the intervention is described in detail elsewhere [20, 21]. In summary, the aim of the intervention is for informal caregivers to increase caregiver resilience to avoid future caregiver burdens. In the intake session, the participants will be familiarized with the program, set goals that they wish to accomplish through their participation, and select four out of the twelve available modules (based on their personal needs and areas of interest). The module themes are provided in Table 1. Each module consists of (1) a short video with experiences/tips from peers, (2) psychoeducation (information) combined with written examples and tips from peers, (3) a reflective assignment, and (4) a 5-step self-management plan. Following the intake, the informal caregivers will complete their selected modules online over 8 to 12 weeks. For each module of the four modules, 2 to 3 weeks are allocated, but participants will be allowed to complete the modules at their own pace because of the self-management principle. After the online period, participants will meet face-to-face with their personal coach to discuss whether their ability to cope with future difficulties and accomplish goals has been improved in an evaluation session. Throughout the intervention, participants are guided by a personal coach, whose main tasks are supporting participants in choosing modules that fit their situation, helping participants identify feasible goals, offering techniques to achieve goals, and providing participants with general constructive feedback on their assignments within the modules. Additionally, they also monitor the completion or incompletion of the assignments within the modules frequently, thus improving intervention adherence.

**Table 1 Tab1:** Themes of the available “Partner in Balance” modules

Module theme	
1	Acceptance
2	Balance in activities
3	Communication with family member and environment
4	Coping with stress
5	Focusing on the positive
6	Insecurities and rumination
7	Self-understanding
8	The changing family member
9	Social relations and support
10	Impact on family life
11	Sexuality and intimacy
12	Combining care with work

This study is a pragmatic trial. Therefore, during the follow-up period other interventions and concomitant care is allowed for participants and will be monitored. The intervention will be provided individually and discontinued or modified if considered necessary by the care professional or participant.

#### Control condition

Participants in the control arm will not receive the PiB intervention but will continue to receive care as usual. More information on usual care in the Netherlands can be consulted in the Dutch guidelines for dementia care [24]. However, in the Netherlands, common dementia care practice varies between regions, but most community-dwelling PwD are cared for by informal caregivers in their own homes. The control arm participants are guided by a dementia case manager. These are trained professionals who visit on fixed moments and offer emotional guidance, help arrange care, and help with navigating the Dutch healthcare environment [25].

### Procedure

The informal caregivers in the intervention and control arm will be assessed at five-time points: baseline assessment (T_0_), after 3 months (T_1_), 6 months (T_2_), 12 months (T_3_), and 24 months (T_4_). The informal caregivers will complete all measurements either via an online survey, by paper post, or via a telephone interview with the researcher depending on their preference. An overview of the enrollment and assessment procedure is shown in Table 2. To ensure the quality of the research, several measures are taken to limit missing data during the conduct of the trial based on recommendations by Little and colleagues [26]. An example was limiting the data collection burden and inconvenience for participants in the development and selection of the questionnaires.

**Table 2 Tab2:**
[figure not shown]
Schedule of enrolment and assessments according to Standard Protocol Items: Recommendations for Interventional Trials (SPIRIT)

*Abbreviations*: *CSES* Caregiver Self-Efficacy Scale, *RUD* Resource Utilization in Dementia, *EQ-5D-5L* EuroQol-5 Dimension Five Levels, *QDRS* Quick Dementia Rating System, *TOPICS-MDS* The Older Persons and Informal Caregivers Survey Minimum DataSet, *HADS* Hospital and Anxiety Depression Scale, *ICECAP-O* Investigating Choice Experiments for the Preferences of Older People, *QOL-AD* Quality of Life in Alzheimer’s Disease, *EDIZ* Ervaren Druk door Informele Zorg, *GAIN* Gain in Alzheimer care Instrument, *IC* Informal caregiver, *PwD* Person with dementia

*Random cluster allocation on the level of the care professional takes place after the completion of the baseline assessment

**Primary outcomes for part 1 (effectiveness)

***Primary outcomes for part 2 (health-economic evaluation)

### Outcomes/measurements

#### Demographics

Demographic characteristics, including age, sex, and educational level of both the caregiver and PwD, will be obtained using a selection of The Older Persons and Informal Caregivers Survey Minimum DataSet (TOPICS-MDS) [27]. This standardized questionnaire measures the general health condition of people with dementia and their informal caregiver. There is a version for the caregiver and for the care receiver.

Demographics of the care professional, such as age, sex, educational level, function, experience with the target group, and care model/style-related characteristics, will be collected using a self-developed questionnaire. In addition, various characteristics of the care organization will also be requested.

#### Primary outcome measures

The primary effectiveness (part 1) outcome is care management self-efficacy which will be measured via the care management self-efficacy domain of the Caregiver Self-Efficacy Scale (CSES) [28]. The domain contains five items that are scored self-rated from 1 (not at all certain) to 10 (very certain). In earlier research, good reliability was demonstrated for the Dutch version of the CSES [21].

For the health-economic evaluation (part 2), the primary outcomes are total care costs and health-related quality-of-life of the informal caregivers and the PwD taken together. The total care use will be obtained using the Resource Utilization in Dementia (RUD) [29]. This assessment measures the care resource use by the informal caregiver (self-rated) and the PwD (proxy-rated). For the caregiver, these resources include informal caregiver time (personal and instrumental activities of daily living and supervision), visits to care professionals, hospitalization, and productivity loss for those with a paid job. The questions on medication usage were not included in this study. For the PwD, it covers accommodation (intermediate form, dementia-specific residential or long-term institutional care), visits to care professionals, hospitalizations, and social care services.

Health-related quality of life of the informal caregiver (self-rated) and the PwD (proxy-rated) will be determined via the EQ-5D-5L assessment developed by EuroQol [30], which measures health-related quality of life on five dimensions: mobility, self-care, usual activities, pain/discomfort, and anxiety/depression on a five-point Likert scale. This scale is recommended as a generic preference-based scale for health-economic analysis in the Dutch guideline for health-economic evaluation [31].

#### Secondary outcome measures

The Hospital and Anxiety Depression Scale (HADS) [32] provides separate scores for depression and anxiety, each with 7 items self-rated on a four-point Likert scale ranging from 0 (not at all) to 3 (a great deal of the time). Total scores range from 0 to 21 per topic, with higher scores indicating more anxiety or depression levels for the informal caregiver. Good reliability was detected in previous research [33].

The Perceived Stress by informal caregiving (EDIZ) (“Ervaren Druk door Informele Zorg”) [34] is a 9-item measurement for informal caregivers to assess self-perceived pressure from informal care. The items are scored on a five-point Likert scale ranging from “no!” to “yes!.” Although the assessment is not as widely applied as the Zarit burden interview (ZBI), the EDIZ was chosen because it contains fewer emotionally sensitive items that might lead to drop-out.

Service-use self-efficacy will be measured via the service-use self-efficacy domain of the Caregiver Self-Efficacy Scale (CSES) [28]. Just as the care management domain, which is used as a primary outcome, this domain contains five items that are scored from 1 (not at all certain) to 10 (very certain).

The Investigating Choice Experiments for the Preferences of Older People (ICECAP-O) [35] measures five important capability attributes of quality of life: attachment, security, role, enjoyment, and control. All items are scored from 1 (no capability) to 4 (full capability), with higher scores indicating a higher overall quality of life for the informal caregiver. The scale has been translated into Dutch [36]. Previous research has indicated that this instrument may be more sensitive to differences between interventions and comparators and that it measures broader outcomes than the EuroQol five dimensions questionnaire [37].

Caregivers’ gain will be measured using the Gain in Alzheimer care Instrument (GAIN) [38]. A total of 10 items are scored on a five-point Likert scale ranging from “disagree a lot” to “agree a lot.” The total summed score ranges from 0 to 40, with higher scores indicating that the caregiver has gained more in dementia caregiving. Previous research has indicated that the GAIN is both reliable and valid among caregivers of community-dwelling PwD [38].

Part of the TOPICS-MDS is perseverance time, which measures how long an informal caregiver is indicated to maintain current care if the caregiving situation remains unchanged. It is rated on a six-point Likert scale ranging from “less than a week” to “more than two years” [27].

The Quality of Life in Alzheimer’s Disease scale (QOL-AD) [39] measures the quality of life for individuals with dementia on 13 separate items on a four-point Likert scale ranging from “poor” to “excellent” and will be proxy-rated. This questionnaire showed adequate reliability in previous research [40].

The execution and independence of the instrumental ADL of the PwD will be proxy-rated through the usage of a selection of the TOPICS-MDS [27].

The Quick Dementia Rating System (QDRS) [41] measures cognitive impairment for people with dementia and consists of six behavioral and four cognitive questions though, in this research, only the latter will be included proxy rated. These four items are scored on a scale from 0 to 3, with higher scores indicating more cognitive impairment. A previous study showed good reliability [41]. In combination with the instrumental ADL measures from the TOPICS-MDS, this will enable a relatively detailed judgment of the severity of dementia.

A self-developed questionnaire will obtain the informal caregivers’ and professionals’ preferences, beliefs, and experiences of e-health or face-to-face contact.

COVID-19 restraint of the informal caregiver will be measured using a self-developed questionnaire. Informal caregivers will answer two statements on a five-point Likert scale ranging from “totally agree” to “completely disagree.”

Care professionals will be asked to keep a logbook on how much time they spent on coaching-related activities (administration, intake session, providing online feedback, and evaluation session) to calculate the costs of the PiB intervention.

### Data management

Data from the assessments will be collected in password-protected electronic case report forms (eCRFs). To promote data quality, all data will be manually checked by a researcher ([name]) for completeness and plausibility shortly after it is received. Missing data or data that does not fall within a plausible range will be verified with the participant via telephone. After the research, the data will be archived in the DISQOVER data repository at Maastricht University.

### Confidentiality

Personal data and measurement data will be stored separately and according to current standards for data security and data privacy. All personal data of potential and enrolled participants are password protected and can only be accessed by authorized persons. Paper documents (e.g., informed consents or paper questionnaires) will be stored in a secure way.

### Sample size

The sample size calculation was based on an earlier short-term effectiveness study of PiB [21] that targeted a similar population and used the CSES as a primary effectiveness outcome measure. With an assumed cluster size of 10 informal caregivers, alpha 0.05, power 0.80, and 25% drop-out at 6 months, the total sample size is 126 participants (with 63 in the control arm and 63 in the intervention arm). However, the sample size will be recalculated based on the CSES after 52 participants have completed their baseline assessment so that the targeted sample size can be adjusted with updated information on the standard deviation.

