#### Part 1: effectiveness

The primary objective is to estimate the effectiveness of the blended care program PiB compared to usual care over 12 months. We hypothesize that the care management self-efficacy in terms of CSES of caregivers who receive PiB will have a significantly better self-efficacy than that of caregivers who only receive usual care. The secondary objective is to explore the effect of PiB on the primary outcome care management self-efficacy at 24-month follow-up and on the secondary outcomes: perseverance time, quality of life, service-use self-efficacy, positive experiences related to informed care, experienced care burden, anxiety, caregiver gains, and depression up to 24-month follow-up.

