### Recruitment

Study participants will be recruited through care professionals with ≥ 1 year of experience with the target population and no prior experience with PiB who are already in contact with the targeted study population (i.e., informal caregivers of a person with early-stage dementia). These care professionals will be recruited from several home care organizations within the Netherlands via the Dutch Dementia network (https://www.dementienetwerknederland.nl/) and via contacts of the Alzheimer Center Limburg. Participating professionals will be asked to screen their caseload for about 1–5 eligible informal caregivers, provide them with introductory information on PiB and, if are interested, send their contact details to the research team. The potential study participants will then be called by the research team and, if they are interested, receive a study information letter and study consent form. Potential participants will be contacted again within 2 weeks. When the caregivers are willing to participate, they will be screened during a short telephone interview to check the inclusion and exclusion criteria. Participation starts after the research team has received written informed consent from the informal caregiver. Participants will be asked separately for consent to reuse their data for future research (participation is thus possible without consent for data reuse).

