### Randomization

Before randomization, the participant will complete the baseline assessment. Then, cluster randomization on the level of the care professionals will be applied. Therefore, professionals and their corresponding set of 1–5 recruited participants will be randomly allocated either to the intervention arm (receives the PiB program in addition to usual care) or to the control arm (only receives usual care) by a spreadsheet random number generator. Because of the shared control arm design, fewer control arm participants need to be recruited than intervention participants. Therefore, in this study, 65% of participants will be allocated to the intervention arm and 35% to the control arm. Stratified randomization [23] will be utilized to ensure that distribution among care professionals within each organization will be as even as possible. Finally, due to variations in the cluster sizes, deviations could occur for the target sample size. In case the allocation diversion is larger than 10% than the desired allocation of 65/35 (e.g., 77% was allocated to the intervention arm at some point during recruitment), the probability to be allocated to the under-allocated arm (e.g., the control arm) will be set to 0.80. The randomization process, enrollment of participants, and assignment of participants to their arms will be executed by the main researcher ([name]). Due to the nature of the intervention in this research, blinding of the participant, care professional, outcome assessor, and data analyst will not be attempted because of pragmatic limitations.

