#### Part 1: effectiveness

Prior to the analysis, the data will be examined for missing data and described. To verify the randomization procedure, potential differences in the baseline characteristics of the intervention and control arm will be examined using t-tests for continuous variables and the chi-squared (*X*^2^) test for categorical variables. A mixed generalized linear model (GLM) will be fitted to the care management CSES score (dependent variable) based on the recommended model of Bell and colleagues [42]. The model will include the following independent variables: trial arm, time (categorically), and the interaction between the trial arm and time. Time will be treated as a categorical variable because Donohue and Aisen [43] discuss that data from early in the trial has less influence in a categorical time model framework. As PIB is aimed at sustainable effects over a longer period, we are interested in the outcome at the end of the trial. Therefore, we believe this approach fits better than treating time as continuous. A link function and distribution family will be chosen that best fits the data (in terms of normality of residuals and linearity). A random intercept will be employed to acknowledge the hierarchical structure of the data (observations clustered within participants, and participants clustered within professionals). An unstructured covariance matrix for residual errors will be applied. If the p-value related to the intervention coefficient is less than 0.05 (2-sided) the intervention will be considered to have a statistically significant effect on the primary outcome, which would confirm our hypothesis. For this analysis, any missing data will be assumed missing at random (MAR) and handled by the mixed model.

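### The sample size of 126 uses clusters of 10 and 6-month drop-out, while the design has clusters of about 1–5 and a 12-month primary objective, so the stated 0.80 is not this design's power.

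*Protocol article*

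**What the plan says.** Sample size takes its inputs from an earlier short-term study of the programme and computes 126 participants, 63 per arm, "With an assumed cluster size of 10 informal caregivers, alpha 0.05, power 0.80, and 25% drop-out at 6 months". It adds that the size will be recalculated on the CSES once 52 participants have completed baseline, "so that the targeted sample size can be adjusted with updated information on the standard deviation".

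The design sections describe other quantities. Recruitment asks each professional to "screen their caseload for about 1–5 eligible informal caregivers". Randomization states that "professionals and their corresponding set of 1–5 recruited participants will be randomly allocated".

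Under Objectives, Part 1, the primary aim is "to estimate the effectiveness of the blended care program PiB compared to usual care over 12 months"; the 24-month effect is secondary. Under Statistical analyses, Part 1, time is categorical because interest lies in the outcome at the end of the trial, and the clustering modelled above the participant is the professional.

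**The concern.** Two inputs to the calculation do not describe the trial being run.

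- **Cluster size.** The professional is both the unit randomised and the clustering level in the model, and brings about 1–5 participants. An assumed size of 10 overstates the design effect for any positive ICC, which makes the target larger than clustering requires.
- **Drop-out horizon.** The 25% allowance stops at 6 months, while the primary objective runs to 12. Cumulative loss at 12 months cannot be lower than at 6 and is likely to be higher, which makes the target too small for a 12-month comparison.

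The two errors pull in opposite directions, by amounts that depend on an ICC and a 12-month loss the article does not give. They would cancel exactly only by coincidence.

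At stake are the recruitment target and the power that will be quoted for the primary comparison. The planned recalculation is the natural place to correct both, but the only updated input it names is the SD.

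**Working it through.** **Inputs from the article.** Alpha is 0.05 (two-sided according to the analysis section), power 0.80, assumed cluster size 10, drop-out 25% at 6 months and N = 126 in equal arms. Equal arms do not conflict with the 65/35 allocation, because the shared control arm supplies the remaining controls. The design's cluster size is about 1–5.

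**Inputs assumed.** ICC 0.01 to 0.10. Cluster sizes uniform on 1–5: mean 3, variance 2, so CV² = 2/9 = 0.222 and CV = 0.47. Loss at 12 months from 25% (no further loss after 6 months) to 44% (the 6-month rate repeated: 1 − 0.75² = 0.4375).

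**Reproducing 126.** This is not possible from the article, because effect size, SD and ICC are not printed. A condensed article may leave them out, and that is not the point here. Only the drop-out step can be checked: 47 / 0.75 = 62.7, rounded up to 63 per arm, which is consistent. I therefore take 126 as giving exactly 0.80 on the plan's inputs. The standardised effect this implies is 2.802 × √(2 × (1 + 9 × ICC) / 47.25), where 47.25 = 63 × 0.75: 0.60 at ICC 0.01, 0.69 at 0.05 and 0.80 at 0.10.

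**Formulas.** The effect and the ICC are then held fixed.

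- Design effect in the plan: DE₁₀ = 1 + (10 − 1) × ICC = 1 + 9 × ICC.
- Design effect for sizes 1–5: DE = 1 + [(1 + 0.222) × 3 − 1] × ICC = 1 + 2.667 × ICC.
- Power at N = 126 with loss a: Φ(2.802 × √(DE₁₀/DE) × √((1 − a)/0.75) − 1.96).
- N for power 0.80: 126 × (DE/DE₁₀) × 0.75/(1 − a).
- Break-even loss, at which 126 still gives 0.80: 1 − 0.75 × DE/DE₁₀.

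**Each error alone.** With 1–5 clusters and loss kept at 25%, power rises to 0.82, 0.89 and 0.93 at ICC 0.01, 0.05 and 0.10. With clusters kept at 10, power falls to 0.74 at 35% loss and 0.68 at 44%, whatever the ICC.

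**Both together, 25% to 44% loss.**

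| ICC | DE₁₀ | DE | Power at 126 | N for 0.80 (approx.) | Break-even loss |
|---|---|---|---|---|---|
| 0.01 | 1.09 | 1.027 | 0.82 to 0.71 | 119 to 158 | 29% |
| 0.05 | 1.45 | 1.133 | 0.89 to 0.78 | 98 to 131 | 41% |
| 0.10 | 1.90 | 1.267 | 0.93 to 0.84 | 84 to 112 | 50% |

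Worked cell, ICC 0.05 and 44% loss: 2.802 × √(1.45/1.133) × √(0.5625/0.75) = 2.744; 2.744 − 1.96 = 0.784; Φ(0.784) = 0.78.

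These powers count completers only. Clustering among the controls taken from the collaborating study, and the matching used to select them, are not modelled.

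**The case against.** The strongest reply is that no harm in a known direction has been shown. The power range straddles 0.80 and the range of N straddles 126. A clear shortfall needs a very low ICC together with high loss; at ICC 0.10 power stays at 0.84 even with 44% lost. This stands. A reader might infer that the trial is underpowered, but the article does not support that: the ICC and the 12-month loss are assumptions, and nothing in the article supports repeating the 6-month rate.

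The completer calculation also overstates the cost of drop-out. The mixed model uses all visits under missing at random, so a participant lost after 6 months still contributes the 3- and 6-month data. That stands too, although only part of the information on a 12-month contrast is recovered.

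Three further inferences go beyond the text:

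- **Clusters of 10 are impossible.** Recruitment speaks of about 1–5, and the cluster sizes of the collaborating study are not given, although its procedures are said to be the same.
- **The recalculation fixes every input except the SD.** The article names the SD and is silent on the rest; it does not freeze them. It therefore does not follow that the new target must be wrong.
- **The arithmetic is wrong.** No such error is shown, and the one step that can be checked is consistent.

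The reply that an article leaves such detail to the full protocol does not remove the point, which concerns inputs the article prints and its own design sections contradict.

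**Conclusion.** The point holds as an inconsistency of inputs and should be fixed. The 0.80 at N = 126 was computed for clusters of 10 and a 6-month loss, and it is not the power of a design with about 1–5 participants per professional and a 12-month primary objective. Under the stated assumptions, completer-based power lies between 0.71 and 0.93 and the N needed for 0.80 between 84 and about 158. These ranges are illustrative, and the sign of the net error is unknown. Reading the primary comparison as the 12-month one is an inference from an objective framed over 12 months and an analysis aimed at the end of the trial, but a fair one. If the recalculation revises only the SD, both mismatches pass into the new target.

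**What to change.** At the planned recalculation, or by re-running it if it has already been done, revise these inputs together with the SD:

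1. The observed mean and variation of participants per professional, in place of 10.
2. An assumed 12-month drop-out, given as a range. Baseline data cannot supply it.
3. The ICC used, with a range. At about 3 per professional, 52 participants come from only about 17 professionals (52/3), so an estimate from these data alone would be imprecise.

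Then restate the power for the 12-month comparison at the resulting size, and say in the Sample size section which inputs the recalculation updates.

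The cost is small: a calculation already scheduled and a few revised sentences. It adds no visits and changes neither randomisation nor analysis. No increase in enrolment is asked for; depending on the ICC and the loss, the revised target could be lower or higher than 126.
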